## Efficacy analysis

The analysis population will be defined as the largest analysis set (full analysis set; FAS), defined as subjects assigned to the study who have consumed the study food at least once and have had at least one efficacy assessment after administration of the study food. Supplemental analyses will also be performed with a per protocol set (PPS) that conforms to the protocol. Hypothesis testing will be two-tailed at the 5% significance level, with two-tailed 95% confidence intervals.

A significance test for the coefficients of the groups will be conducted using a model in which the DAS28-ESR at the end of the intervention for the primary endpoint is the objective variable, the group (control or intervention) is the explanatory variable, and the value of the DAS28-ESR at week 0 is the covariate. In order to confirm the robustness of the results associated with the completion of missing values by LOCF, a mixed-effects model will be used as a supplementary analysis for the primary endpoint. In this case, the normality of the DAS28-ESR at the end of the intervention is checked by histogram, and if normality is not found, the variable is transformed by log transformation or other methods to follow a normal distribution before being used in the analysis. As a secondary analysis, when the objective variable is DAS28-ESR, the interaction between group (control, intervention) and time point (12 weeks, 24 weeks) and between group and time point will be used as explanatory variables, and the analysis will be conducted using a mixed-effects model with the value of DAS28-ESR at week 0 as the covariate and subjects as the variable effect, and the correlation structure of time points will be unstructured.

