# Study aims

Object disease patients: 80 female RA patients who met the 2010 ACR/EULAR classification criteria. Test food: Test tablets containing Brazilian propolis

Evaluation items：

・Anthropometry: height, weight, waist circumference

・Disease activity：DAS28-ESR・DAS28-CRP・SDAI・CDAI

・ADL：mHAQ

・Laboratory data: General items（WBC, RBC, Hb, Ht, Plt, AST, ALT, γ-GTP, T-Bil, Cre, BUN, CRP, ESR, RF, TP, Alb, T-chol, HDL-chol, TG, Na, Cl, K, Mg, P, Ca, FBS, special items（anti CCP antibody, MMP-3, IL-6, IL-17, IL-10）

・Blood pressure

・Lifestyle survey: smoking status, alcohol consumption, exercise habits, sleep time, supplement use and type

・QOL:SF－36

・Objective arthritis assessment: sonographic examination of joints

　Eighty female RA patients with moderate disease activity by DAS28-ESR will be divided into two groups: 40 patients treated with Brazilian propolis (P group) and 40 patients treated with placebo balls (C group). In doing so, allocation will be by double-blind randomization using a stratified replacement block method, with facilities in strata. The test food is manufactured at Yamada Bee Company, Inc., Ltd. for 40 people in each group, plus 5 people in the reserve group, for a 3-month supply of 5 tablets per day x (84 days + 7 days in reserve) x 45 people = 2,0475 tablets. This is one set and we plan to make two sets for 6 months. The P group will take 5 tablets of the test diet containing Brazilian propolis (508.5 mg as P) per day, and the C group will take 5 tablets of the placebo diet without Brazilian propolis per day. In both groups, DAS28-ESR will be compared at 0, 12, 24, and 36 weeks, and the above evaluation items will also be compared.

The purpose of this study is to clarify whether Brazilian propolis has an suppressive effect on disease activity not only in mouse RA models but also in RA patients.

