# Objective number of cases and evidence of setting

## Objective number of cases

Number of participating institutions: 3 institutions, Objective number of cases: 80

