## Evidence of setting

　There are no clinical trials in which propolis containing this test food has been administered to patients with RA. In a similar study examining the effect of Mediterranean diet intervention on RA patients (Ann Rheum Dis 2003: 62: 208-214), the mean difference in DAS28-ESR between 25 patients in the control group and 26 patients in the intervention group at 12 weeks was 0.4 points (statistically significant difference between the two groups at 12 weeks). However, the study did not use the DAS28-ESR as a subject eligibility criterion, and there was concern about the large variability in disease activity among study participants. In this study, the entry criterion is limited to moderately active disease from the viewpoint of clinical disease management, and the intervention effect of the test food on DAS28-ESR is expected to be the same as or greater than that of the above study. Therefore, the following hypotheses were designed based on the data from the cohort study of RA patients and non-RA controls that has been conducted in Japan since 2010 by a research group including the principal investigator. Of the 182 rheumatoid arthritis patients who continued to participate in our cohort study, the TOMORROW Study, as of 2016, 67 RA patients with moderately active disease had a mean change in disease activity of -0.22 under standard treatment over 1 year. We assume that the add-on effect of propolis is -0.5. Assuming σ (standard deviation of expected outcome) = 0.78, at least 39 subjects in each group would be required to detect δ (the value we would like to see as the difference in DAS28-ESR after 24 weeks between the two groups) = 0.5 at a significance level of α = 0.05 with 80% power by a two-sample t-test. In consideration of the burden on subjects to participate in the study, we set the objective to have 40 subjects in each group for a total of 80 subjects, considering that there would be few dropouts during the study period.

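### Randomisation is stratified by facility but the primary model leaves facility out; if facility predicts outcome after baseline, the test is conservative and some attainable power is given up

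*Protocol*

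**What the plan says.** Protocol section 2 (Study aims) states that "allocation will be by double-blind randomization using a stratified replacement block method, with facilities in strata". Section 15.1 gives the size of the trial: "Number of participating institutions: 3 institutions, Objective number of cases: 80".

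Section 14.2 (Efficacy analysis) names the terms of the primary model. The outcome is DAS28-ESR at the end of the intervention, and "the group (control or intervention) is the explanatory variable, and the value of the DAS28-ESR at week 0 is the covariate". The mixed model in the same section has group, time point (weeks 12 and 24) and their interaction, and is described as a "mixed-effects model with the value of DAS28-ESR at week 0 as the covariate and subjects as the variable effect". Neither model contains facility.

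Section 14.3 applies the primary method to DAS28-CRP, SDAI, CDAI, SF-36, mHAQ and joint sonography, so these analyses also lack the term. The protocol gives no reason for leaving it out.

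**The concern.** Blocking within facility balances the arms within each facility. Differences between facilities therefore drop out of the true sampling variance of the treatment contrast. A model without facility does not know this and leaves those differences in the residual. If they are real, the reported standard error exceeds the true one, the confidence interval is too wide, and the test rejects less often than its nominal level.

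Facility differences are plausible here. DAS28-ESR depends partly on palpated joint counts. ESR is not among the tests that the protocol lists for the central laboratory. Section 7.5 lets background treatment change when disease is not adequately controlled, so local practice could affect week-24 values.

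What is at stake is precision. Section 15.2 requires 39 per group and plans 40, with no numerical allowance for dropout, so precision that costs no patients is worth having.

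**Working it through.** **Inputs from the protocol.**
- Difference δ = 0.5, two-sample t-test, 80% power (15.2).
- SD 0.78: "Assuming σ (standard deviation of expected outcome) = 0.78, at least 39 subjects in each group would be required" (15.2).
- Planned n = 40 per group (15.2).
- Two-sided 5% level: "Hypothesis testing will be two-tailed at the 5% significance level, with two-tailed 95% confidence intervals" (14.2).
- Three facilities as strata (2 and 15.1).

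**Assumptions, not in the protocol.**
- The share f of the residual variance of week-24 DAS28-ESR (after baseline) that lies between facilities is varied over 0, 2, 5, 10 and 20%.
- Facility sizes are 24/28/28. Section 7.7 gives only supply numbers, 26/32/32. Scaled from 90 to 80 these are 26 × 80/90 = 23.1 and 32 × 80/90 = 28.4.
- Blocks are of size 4.
- Residual SD after baseline is 0.78, which credits the baseline covariate with no gain.

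**Step 1: reproduce the plan's figure.** n per group = 2(1.960 + 0.842)² × 0.78²/0.5² = 2 × 7.85 × 2.4336 = 38.2, rounded up to 39. The stated 39 reproduces. Power by the normal formula is 80.8% at 39 and 81.8% at 40. By the exact noncentral t it is 79.8% and 80.8%.

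**Step 2: what omitting the stratum does, by formula.**
- Reported variance of the treatment difference: about 2σ²/n.
- True variance under blocking within facility: about 2σ²(1 − f)/n.
- Ratio of reported to true standard error: 1/√(1 − f), which is 1.010, 1.026, 1.054 and 1.118 for f = 2, 5, 10 and 20%.
- Type I error: 2Φ(−1.96/√(1 − f)), which is about 4.8, 4.4, 3.9 and 2.8%.
- n per group for 80% power with facility in the model: 38.2(1 − f), rounded up, which is 38, 37, 35 and 31.

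**Step 3: check by simulation.** There were 8,000 trials per setting, with baseline uniform on 3.2 to 5.1 and fixed facility effects. ANCOVA was fitted to the same data with and without facility.

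| Facility share f | Reported SE, facility omitted | True SE, facility omitted | Type I error, omitted | Power, omitted | Power, included | Change (points) |
|---|---|---|---|---|---|---|
| 0% | 0.1746 | 0.1740 | 5.0% | 81.1% | 80.8% | -0.3 |
| 2% | 0.1752 | 0.1731 | 4.7% | 80.6% | 81.2% | +0.6 |
| 5% | 0.1751 | 0.1717 | 4.3% | 80.9% | 82.3% | +1.4 |
| 10% | 0.1753 | 0.1657 | 3.7% | 81.7% | 84.5% | +2.8 |
| 20% | 0.1754 | 0.1575 | 3.0% | 82.8% | 88.3% | +5.5 |

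The reported standard error is too large by about 1, 2, 6 and 11% at shares of 2, 5, 10 and 20%. With facility in the model, reported and true standard errors agree closely and type I error is 4.7 to 5.0% at every share. The Monte Carlo error is about √(0.05 × 0.95/8000) = 0.24 points for type I error and √(0.8 × 0.2/8000) = 0.45 points for each power figure. Simulation and formula agree in direction and closely in size.

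**The case against.** The strongest reply is that nothing here is shown to go wrong. The loss exists only if facility predicts week-24 DAS28-ESR once week 0 is in the model, and the protocol gives no figure for that. Stable differences in assessors or patient mix would already show in the week-0 score, which is the covariate. Entry is limited to a narrow band of disease activity on stable DMARDs. Both features favour a small share, so the 10% and 20% rows are scenarios, not expectations. This stands, and the size must be stated as conditional.

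A reader might infer that the trial falls short of its planned 80% power. The documents do not support that. The sample size rests on an unadjusted t-test, and the model without facility keeps 80.6 to 82.8% power over the whole range examined. The loss is measured only against a better model. Baseline adjustment may also lower the residual SD below 0.78, so the margin of 40 over 39 is not the full account of the trial's slack.

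It could also be said that a statistical analysis plan may add the term. But the protocol does not leave the model open: it names the covariate, so adding facility later would depart from the written primary analysis.

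The secondary endpoints carry less weight, because section 14.3 treats them as exploratory.

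**Conclusion.** The mismatch is real: facility is a stratum in the randomisation and is absent from every efficacy model that the protocol fixes. Its consequence is conditional and runs in one direction. If facility is prognostic after baseline, the analysis is conservative and gives up power that the design has already made available. If it is not, nothing material is lost either way.

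Over the assumed range, adding facility changes power by -0.3 to +1.4 points at shares of 0 to 5% and by +2.8 to +5.5 points at 10 to 20%. In sample-size terms, shares of 5 to 10% are worth 2 to 4 patients per group (39 down to 37 or 35). These figures also rest on the assumed facility sizes, blocks of 4 and a residual SD of 0.78.

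A reader might infer a validity problem. There is none: the omission neither biases the treatment estimate nor inflates type I error, and it does not make the sample-size calculation wrong. The point is a minor to moderate gain in efficiency, worth taking because it is nearly free.

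**What to change.** In section 14.2, add facility as a three-level fixed effect to the primary ANCOVA, so that week-24 DAS28-ESR is modelled on group, week-0 DAS28-ESR and facility. Add the same term to the mixed model. State in section 14.3 that the efficacy secondary models handled by the primary method include it too. Make the change before unblinding, so that the model is not chosen after results are known.

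The cost is one phrase and 2 degrees of freedom: with all 80 patients, residual degrees of freedom in the ANCOVA go from 80 − 3 = 77 to 80 − 5 = 75. No new data are needed, because facility must be known to run the stratified allocation. If facility turns out not to matter, the price is about 0.3 power points in the simulation, which is negligible.

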## Inclusion criteria

　Patients who meet all the following criteria should be selected for inclusion.

1. RA patients meeting the 2010 ACR / EULAR classification criteria (irrespective of disease duration)
2. Age: Patients who are between 30 and 70 years old at the time of obtaining consent
3. Gender：Female
4. Moderate disease activity (DAS28-ESR is greater than 3.2, less than or equal to 5.1)
5. After receiving sufficient explanation for the participation of this study, patients who obtained document consent by the patient's free will with sufficient understanding.
6. Administration of bDMARDs and csDMARDs is constant over 12 weeks before intervention
7. The dose of NSAID and steroid (predonisolone equivalent 10 mg / day or less) dose is also constant for 12 weeks or more before consent acquisition
8. Outpatient

［Evidence of setting］

1) Because this is a study of RA patients and the duration of illness is not expected to

affect the results of the study.

2) This is due to the epidemiological background of RA. Because most outpatients are between

30 and 70 years of age.

3) We restricted the study to females, much of the population, so as not to be influenced by

gender.

4) Because we believe that if the disease activity is below low disease activity, therapeutic target is reached, and high disease activity is not the target of the health food.

5）From an ethical perspective.

6)-7) To exclude the effect of medication on disease activity, as it has a strong impact on

patients treated with medications for RA.

8) To perform disease assessment every three months.

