# Observation and examination items and schedule

The following surveys will be conducted according to the timetable

1. Patient's background

　Medical record number, patient name, gender, date of birth, comorbidities, medical history, current medical history, previous treatment, concomitant medications (concomitant therapy and current treatment details), lifestyle (smoking status, alcohol consumption, exercise habits, sleep time, supplement use and type). However, medical record numbers and patient names are not entered into the REDCap (case report form).

1. Confirmation of intake of test foods

　The intake status during the study period will be assessed in percentage and recorded in REDCap. Participants will return all samples, including unused packaging materials, to the implementing medical institution at each visit. The CRC calculates the intake rate based on the number of tablets distributed and returned. For each case, the intake of the test food from the day after the previous visit to the day of the visit will be investigated and compliance with the intake will be requested.

1. Confirmation of subjective symptoms and other findings, evaluation of disease activity

Based on the questionnaire, palpation, and laboratory data, disease activity is quantified according to the following formula.

DAS28-ESR = 0.56 × √28TJC + 0.28 × √28SJC + 0.76In(ESR) + 0.014 × GH-VAS

DAS28-CRP = 0.56 × √28TJC + 0.28 × √28SJC + 0.36In(CRP × 10 + 1 ) + 0.014 × GH-VAS + 0.96

SDAI = 28TJC + 28SJC + PtGH-VAS(patient) + DrGH-VAS(physician) + CRP (mg/dl)

CDAI = 28TJC + 28SJC + PtGH-VAS(patient) + DrGH-VAS(physician)

1. Confirmation of adverse events and side effects: Describe in the medical record and case report the details, including abnormalities in various laboratory data, time of occurrence and disappearance, severity, treatment, outcome, assessment of severity, and relationship to the study food, and follow up as necessary. The severity is defined as 1) mild: administration can be continued without treatment, 2) moderate: administration can be continued with some treatment, and 3) severe: administration should be stopped or discontinued.
2. Height, weight, and waist circumference
3. Blood pressure and pulse rate
4. Hematological tests

WBC, RBC, Hb, Ht, Plt

1. Blood biochemistry test

AST, ALT, γ-GTP, T-Bil, Cre, BUN, CRP, ESR, RF, TP, Alb, T-chol, HDL-chol,TG, Na, Cl, K, Mg, P, Ca, FBS

1. Other specific tests

・anti-CCP antibody、MMP-3、IL-6、IL-17、IL-10

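### Background bDMARD use is recorded before treatment but is neither a randomisation stratum nor a covariate in the (valid) primary model; prespecifying it would be a cheap, optional gain

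*Protocol*

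**What the plan says.** Section 14.2 (Efficacy analysis) regresses DAS28-ESR at the end of the intervention on two terms: "the group (control or intervention) is the explanatory variable, and the value of the DAS28-ESR at week 0 is the covariate". It has no term for background medication. "Hypothesis testing will be two-tailed at the 5% significance level".

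On allocation, section 2 (Study aims) states that "allocation will be by double-blind randomization using a stratified replacement block method, with facilities in strata". No other stratification factor is named.

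On medication, section 5.1 requires bDMARD and csDMARD treatment to be constant over the 12 weeks before intervention, with a matching rule for NSAIDs and steroids. The reason given for these two criteria begins "To exclude the effect of medication on disease activity, as it has a strong impact on" and goes on to refer to patients under drug treatment for RA. Section 7.5 allows biologics at a constant dose. Section 8 lists, among the background items, "concomitant medications (concomitant therapy and current treatment details", and its timetable places that check at the pre-observation visit.

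The sample size in section 15.2 rests on an unadjusted comparison made "at a significance level of α = 0.05 with 80% power by a two-sample t-test". The planning difference is 0.5 points and the SD 0.78, which the protocol turns into a group size as follows: "Assuming σ (standard deviation of expected outcome) = 0.78, at least 39 subjects in each group would be required". The plan is for 40 per group.

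**The concern.** The trial mixes patients who needed a biologic with patients who did not. The 12-week rule keeps a newly started drug from contaminating the comparison. It does not make the two kinds of patient alike in how their score moves over the next 24 weeks. Two women with the same week-0 score, one on a biologic and one not, are identical to the model.

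If drug class does predict the later course at equal baseline, two things follow. The variance it explains stays in the error term, and a chance imbalance between groups moves the primary estimate. The sample size has one patient per group to spare over the calculated 39, and no dropout rate is stated. If a visible imbalance appears after unblinding, an adjustment chosen then would be post hoc. The covariate is already collected.

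**Working it through.** **Inputs from the protocol.** Difference 0.5, SD 0.78, two-sided 5% level, 80% power, 39 required and 40 planned per group (15.2); model with group and week-0 score (14.2).

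**Assumed, because the protocol gives no figure.** Share of bDMARD users p = 30% or 50%. Difference b between users and non-users at week 24, at equal week-0 score, from 0 to 0.7. SD 0.78 is taken as the residual SD given week-0 score, which is cautious because the covariate should lower it.

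**Step 1: the plan's own figure.** n = 2 × (1.960 + 0.842)² × 0.78² / 0.5² = 38.2, so 39 per group. It reproduces. The calculation takes no credit for any covariate, so the missing term causes no sample-size error.

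**Step 2: current model at 40 per group.** SE = 0.78 × √(2/40) = 0.174. Noncentral-t power with 77 degrees of freedom is 80.8%.

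**Step 3: model with the bDMARD term.** The share of residual variance explained is R² = b² p(1 − p) / 0.78². The SE becomes 0.78 × √(1 − R²) × √(2/40) × √(1 + 1/76), where the last factor, 1.0066, allows for chance collinearity; 76 degrees of freedom remain.

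| b | R² (30% / 50%) | SE (30% / 50%) | Power (30% / 50%) | Change in points |
|---|---|---|---|---|
| 0 | 0 / 0 | 0.176 / 0.176 | 80.3% / 80.3% | -0.5 / -0.5 |
| 0.2 | 0.014 / 0.016 | 0.174 / 0.174 | 80.8% / 80.9% | 0.0 / +0.1 |
| 0.3 | 0.031 / 0.037 | 0.173 / 0.172 | 81.5% / 81.7% | +0.7 / +0.9 |
| 0.5 | 0.086 / 0.103 | 0.168 / 0.166 | 83.7% / 84.3% | +2.9 / +3.5 |
| 0.7 | 0.169 / 0.201 | 0.160 / 0.157 | 87.0% / 88.2% | +6.2 / +7.4 |

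Break-even is at a difference of about 0.2.

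**Step 4: sensitivity to the residual SD.** If week-0 score correlates 0.5 with the outcome (assumed), the residual SD is 0.78 × √(1 − 0.25) = 0.675. The current model then has 90.5% power, and the term changes it by -0.4 points at R² = 0, +1.0 at 0.05, +2.4 at 0.10 and +4.8 at 0.20.

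**Step 5: chance imbalance.** A gap of 20 percentage points is 8 patients out of 40. With two independent binomial counts, the exact probability of a gap at least that large, in either direction, is 6.7% at p = 30% and 9.3% at p = 50%. A 20-point gap shifts the unadjusted estimate by 0.20 × 0.3 = 0.06 or 0.20 × 0.5 = 0.10. Against the design difference of 0.5 that is 12% or 20%; both shifts are below one SE (0.174). Stratifying by facility would make large gaps rarer to the extent that bDMARD use differs between facilities.

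**The case against.** The strongest case is that nothing here is wrong. Baseline-adjusted ANCOVA is a standard primary model, the randomised comparison is unbiased, the test keeps its level, and chance imbalance in an omitted covariate is already reflected in the standard error. The design promised 80% power from an unadjusted test, and a baseline-adjusted model should do at least as well. Further covariates may be left to a statistical analysis plan, which is not at hand. All of that stands.

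A reader might infer from section 5.1 that the protocol itself names drug class as prognostic. It does not. The sentence concerns RA medication in general and explains why dosing must be stable. It does not single out bDMARDs, and it does not say that drug class predicts week 24 given week-0 score.

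A reader might also infer that precision is certainly being lost. That does not follow either. Week-0 DAS28-ESR is measured on the stable therapy, so it already carries much of the drug effect. Only a residual effect on the 24-week course matters, and the documents give no evidence of its size. A residual difference of 0.5 would equal the whole assumed propolis effect, and 0.7 would exceed it.

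What remains is an asymmetry: the possible loss is about half a power point, and the possible gain is several.

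**Conclusion.** The primary analysis is valid. Its covariate set could be improved at almost no cost, and this is an optional recommendation, not the correction of an error. The effect on power runs from about -0.5 points (drug class not prognostic) through +1 (difference 0.3) to +3 to +4 (difference 0.5) and +6 to +7 (difference 0.7). These figures rest on an assumed 30-50% bDMARD share, residual SD 0.78, 40 evaluable patients per group and a true effect of 0.5. The larger gains need a class difference that nothing in the protocol documents. The more dependable benefit is that a bDMARD imbalance, if one occurs, would be handled by a rule fixed in advance.

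Two neighbouring matters are separate. Facility, the stratification factor, is also absent from the primary model. Medication changes during the 24 weeks, which section 7.5 permits in some circumstances, would not be dealt with by a baseline term.

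**What to change.** In section 14.2, before unblinding, add bDMARD use at week 0 (yes/no, derived from the recorded concomitant medication) as a prespecified fixed covariate in the primary ANCOVA and in the mixed-effects model. Report the current model, with group and week-0 DAS28-ESR only, as a sensitivity analysis. Section 14.3 analyses the efficacy secondary endpoints in the same way as the primary one, so state there whether the term carries over.

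Cost: one sentence of text, no new data and one degree of freedom. If drug class turns out not to be prognostic, the SE rises by about 0.7% (√(1 + 1/76) = 1.0066) and power falls by about half a point.
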